### Randomization

Eighteen daycare centres (clusters) that agree to participate will be randomly assigned to one of three groups: i) ABC program delivered at daycare centre only (n = 6; DC), ii) ABC program delivered at daycare plus a home component (n = 6; DC + HOME) or, iii) regular daycare curriculum (n = 6; COM).

Because daycare centre size, language of delivery, and season may influence the outcomes of interest, randomization will be stratified based on these variables. Small-medium daycare centres will be defined as those serving 10 to 20 children in our 3- to 5-year-old targeted age range, those enrolling 21 or more preschoolers will be considered large. To take into account possible seasonal effects on PA, the trial will be stratified by season: 8 sites will be randomized in the Spring of 2013 (3 in DC, 3 in DC + HOME, and 2 in COM)), 7 in the Fall of 2013 (2 in DC, 2 in DC + HOME, and 3 in COM), and 3 will be randomized in the Fall of 2014 (1 in DC, 1 in DC + HOME, and 1 in COM). The randomization sequence will be computer generated by a data manager at the Clinical Research Unit at the Children’s Hospital of Eastern Ontario, who is not affiliated with this trial. Before running the randomization program, the data manager will document the study ID and daycare centre size, and season. After running the program, the data manager will document the group assignment and then inform the study coordinator of the assignment. To ensure adequate allocation concealment, the randomization sequence list will be kept centrally with the data manager at the Clinical Research Unit. It will not be accessible to members of the study team and subjects and only be activated when a centre is eligible to be randomized.

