**CONSORT flow diagram.**

### Participants, inclusion/exclusion, and recruitment

#### Daycare centres

All licensed daycare centres in the National Capital Region (NCR) that serve children between the ages of 3 and 5, with an enrolment of >20 children in this age range, and provide service in either English or French, are eligible to participate. Daycare recruitment will commence with an initial letter mailed out to the directors of all daycare centres within the NCR, requesting that the directors contact the research coordinator for further information related to the study if they are interested in taking part. Daycare directors who agree for their site to participate in the trial are committing to modify their curriculum accordingly and support their staff in facilitating the required changes if they are randomized to the intervention arm and control groups must agree to allow study personnel to visit their facilities for planned assessments.

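### Language is a named stratifier missing from the pre-randomization record, the size stratum conflicts with eligibility, and the pre-announced 1/1/1 split makes the last cohort predictable if centres are released singly

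*Protocol article*

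**What the plan says.** All places are in the protocol article.

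- **Stratifiers** (Randomization): "Because daycare centre size, language of delivery, and season may influence the outcomes of interest, randomization will be stratified based on these variables".
- **Record made before the program is run** (Randomization): "the data manager will document the study ID and daycare centre size, and season". Language is not in this list.
- **Size levels** (Randomization): "Small-medium daycare centres will be defined as those serving 10 to 20 children", and "those enrolling 21 or more preschoolers will be considered large".
- **Centre eligibility** (Daycare centres): a centre must have the required enrolment, stated as "with an enrolment of >20 children in this age range", and "provide service in either English or French".
- **Cohort quotas** (Randomization): Spring 2013 has 8 centres split 3/3/2 over DC, DC + HOME and COM. Fall 2013 has 7 split 2/2/3. For the last cohort, "3 will be randomized in the Fall of 2014 (1 in DC, 1 in DC + HOME, and 1 in COM".
- **Release** (Randomization): the list is held centrally by a data manager who is not affiliated with the trial. It will "only be activated when a centre is eligible to be randomized". After the run, the study coordinator is told the assignment.
- **Timing** (Trial status): the first two cohorts have been randomized and followed up. The third is planned for September 2014.

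**The concern.** The article sets out its allocation procedure in some detail, and the parts do not fit together.

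First, a stratified scheme needs each stratifier as an input when the program is run. Two of the three are listed and language is left out.

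Second, one of the two size strata can contain no centre that meets the eligibility criterion.

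Third, the text claims adequate concealment on the ground that the list is kept centrally. Central storage protects a list from being read. It does not stop someone who knows a small fixed quota and the assignments already made from working out what remains.

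The primary contrast compares 6 DC centres with 6 COM centres. With so few clusters, an imbalance in a factor that the authors themselves consider influential can matter, and the covariates named for the primary model (age, sex, extra-curricular activity) do not include language, size or season. Foreknowledge of a centre's arm is a recognised route to selection bias in cluster trials.

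**Working it through.** **1. Quotas against the stated totals.** DC 3 + 2 + 1 = 6; DC + HOME 3 + 2 + 1 = 6; COM 2 + 3 + 1 = 6; cohorts 8 + 7 + 3 = 18. The plan's own figures reproduce and agree with each other.

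**2. Stratifiers against the recorded items.**

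| Named stratifier | Documented before the run? |
|---|---|
| Centre size | yes |
| Season | yes |
| Language of delivery | not listed |

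**3. Cells.** Inputs: 2 languages, 3 cohorts, and 2 size levels as defined under Randomization.

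- Eligibility rule set aside: 2 × 2 × 3 = 12 cells, 18/12 = 1.5 centres per cell. Per cohort the four size-by-language cells average 8/4 = 2.0, 7/4 = 1.75 and 3/4 = 0.75 centres.
- Eligibility rule applied: every eligible centre is in the large stratum, so size has one level. This leaves 1 × 2 × 3 = 6 cells, 18/6 = 3.0 centres per cell. Per cohort the two language cells average 8/2 = 4.0, 7/2 = 3.5 and 3/2 = 1.5 centres.

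On the second count, the first two cohorts average more than three centres per language cell. The third does not: with one centre per arm, language can be balanced only if all three centres share one language.

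**4. Predictability of the third cohort (1/1/1).** Assume that centres are released singly, each result is known before the next release, and the quota is known. The chance of guessing the arm correctly is 1/3 for the first centre, 1/2 for the second and 1 for the third. Expected correct guesses: 1/3 + 1/2 + 1 = 1.83 of 3, against 3 × 1/3 = 1.0 if each arm were concealed. If all three are allocated in one run, the excess disappears.

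**5. The same calculation over all cohorts.** Always guess the arm with most places left, and average over all random orders of each quota. Expected correct guesses are 4.45 of 8, 4.02 of 7 and 1.83 of 3, in total 10.31/18 = 57%. The comparator matters. One list of 6/6/6 released singly, with no season quotas, already gives 8.75/18 = 49%. The season quotas therefore add about 8 percentage points, not the 24 suggested by setting 57% against 33%.

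**6. Chance imbalance in language if it is not used (illustrative).** The article gives no count of French centres, so F of 18 is an assumption, and the season quotas are ignored. With a, b and c the numbers of French centres in DC, COM and DC + HOME,

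P(|a − b| ≥ 2) = Σ C(6,a)·C(6,b)·C(6,c) / C(18,F), over a + b + c = F with |a − b| ≥ 2.

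| F | Calculation | Probability |
|---|---|---|
| 2 | 30/153 | 20% |
| 4 | 960/3,060 | 31% |
| 6 | 6,976/18,564 | 38% |
| 9 | 19,560/48,620 | 40% |

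**The case against.** The case on the other side has weight, and parts of it stand.

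*Language.* The article says outright that randomization is stratified on language. The later list is one sentence about record-keeping in a condensed article. This stands to the extent that the omission does not prove that language was never captured or used. It does not remove the mismatch between the two statements.

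*Too many cells.* A reader might infer that 18 centres face 12 cells, so that a cell never fills one block of three and stratification cannot work. The document does not support this. Under its own eligibility rule at most 6 cells remain and the first two cohorts average 4.0 and 3.5 centres per cell. No block size or algorithm is stated either. What remains is that one stratifier is empty as written.

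*Predictability throughout the trial.* A reader might take the 57% as a measure of the whole trial. That needs single release and quotas known in advance in all three cohorts. Fifteen of the 18 centres were already randomized when this text was written, and the uneven 3/3/2 and 2/2/3 splits may simply record what happened. The Trial status section also speaks of cohorts being randomized, which fits allocation in one batch. This objection stands for the first two cohorts. For the third, the quota is announced beforehand and the release wording refers to a single centre.

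*The coordinator steering centres.* A reader might infer that the coordinator could choose which centre is put forward next. No passage says so. Interested directors refer themselves to a research coordinator and commit to either kind of arm beforehand. Whether that role is the study coordinator who receives the assignments is not stated.

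**Conclusion.** The concern holds in a limited form.

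- **Language:** the stated procedure does not support the stated stratification. This is an internal inconsistency, not proof that language was ignored. Were it ignored, DC and COM would differ by two or more French centres with a probability of 20% to 40% for 2 to 9 French centres. That range is illustrative only, and no effect on MVPA follows from it.
- **Size:** void as a stratifier if the eligibility rule is applied. The Daycare centres and Randomization sections must be reconciled.
- **Concealment:** for the three Fall 2014 centres, single release under the published 1/1/1 split makes the second allocation a 1-in-2 guess and the third certain. This rests on reading the activation sentence as one centre at a time, and it vanishes if the cohort is allocated together.
- **First two cohorts:** a weakness in concealment there would need quotas known beforehand and sequential release. The document establishes neither.

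The exposed part is 3 of 18 centres. The point still merits action, because that cohort is not yet randomized and the remedy is nearly free.

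**What to change.** 1. Add language of delivery to the items that the data manager records before the program is run.
2. Allocate the three Fall 2014 centres in a single run, as a simple random permutation of one centre per arm, after all three have consented and been declared eligible. State this in place of the activation wording. Restricting the draw to the best-balanced permutations is not advised: only 3! = 6 exist, and with 15 assignments already known the restriction could make a centre's arm nearly deterministic.
3. Reconcile the enrolment criterion with the size strata, and state which centres were in fact admitted.
4. For the first two cohorts, report which stratifiers were actually applied, whether the quotas were set beforehand, and whether centres were released singly or as a cohort. Claim language and size stratification only where it was used.

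The cost is a few sentences and a short allocation run. The one practical drawback is that the first centres to consent in the last cohort must wait for the third.

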#### ABC intervention (common to DC and DC + HOME)

The ABC intervention, designed to increase PA and reduce sedentary behaviour, will consist of two 3-hour workshop training sessions conducted by a master trainer with experience in promoting PA in preschoolers. The training workshops will target the daycare providers of 3- to 5-year-old children assigned to both the DC and DC + HOME arms of the intervention trial. The first workshop will focus on the importance of PA and movement skills for preschool-aged children, understanding structured and unstructured play, familiarization with the intervention tools and broad practicalities of implementing ABC in daycare centres, and include demonstrations of activities related to movement skills. The second workshop will focus on the goals of i) providing opportunities for light, moderate, and vigorous PA for at least 15 minutes per hour while the children are in care, ii) providing daily outdoor time for PA when possible, iii) providing a combination of developmentally appropriate structured and unstructured PA experiences, iv) becoming an active participant and joining children in PA, as well as providing verbal guidance and encouragement, v) integrating PA into activities designed to promote cognitive and social development, vi) providing both indoor and outdoor environments with a variety of portable play equipment and adequate space per child, vii) avoiding the punishment of children for being active, and viii) avoiding disciplining/punishing children by withholding PA. The training will work on overcoming barriers to facilitating PA, understanding the range of movement skills, and using everyday materials to facilitate PA and active play.

In addition, each daycare centre in the intervention groups will be given the ABC resource training manual, recommended activity program outline with log sheets, music developed for PA with an outlined guidebook, and a starter kit of equipment that will form the basis of training for the daycare providers and the intervention itself. The manual is compiled with various ways providers can get children active in structured and unstructured physical activities, some of which target motor skill development. Our team will provide the educators with weekly schedules that suggest a set of activities, drawn from the ABC manual, that can be incorporated into the daily curriculum with the aim of meeting the Canadian Society for Exercise Physiology guidelines of accumulating at least 180 minutes of PA at any intensity spread throughout the day for preschool-aged children [37] and at least 60 minutes of MVPA for the children aged 5 years [53]. Additionally, these guidelines also suggest limiting the children’s sedentary time and minimizing screen time to less than 60 minutes a day for children aged 3 to 4 years, and limit recreational screen time to less than 2 hours for children aged 5 years [54]. These suggested activities have been broken down as locomotor skills, manipulative motor skills, and moving to music, shapes, and creative play. The program includes 60 minutes of structured activities, with the largest percentage (50%) of time spent on locomotor skills, as those are the higher intensity activities (such as running to play tag) and will more likely increase MVPA. Manipulative motor skill activities aid in developing gross motor skills which are important for major body movement such as walking, maintaining balance, coordination, jumping, and reaching. In addition to participating in PA, children with poor gross motor skills, may also have difficulty sitting in an alert position to watch classroom activity and writing on a blackboard. As a result, the second greatest percentage of time within the program is allocated toward gross motor development (33%) and 17% is devoted to creative play. On a daily basis, daycare providers will be asked to track facilitated physical activities using a simple pre-developed program tracking log sheet. Bi-monthly follow-up support or ‘booster’ sessions will also take place during regular hours within intervention daycare centres. These will be multi-dimensional, and include i) in-centre, ABC project staff-guided, structured PA sessions engaging both preschoolers and providers, ii) goal setting and iterative action planning regarding intervention delivery, and iii) performance monitoring and feedback related to implementation successes and, where relevant, overcoming barriers, troubleshooting, and problem solving.

#### Home environment

While children who attend licensed daycare centres often spend the majority of their waking hours in these environments, the importance of the home environment cannot be overlooked since parents are primary role models and therefore carry considerable influence in the development of their children’s behaviour. Thus, those daycare centres assigned to the DC + HOME arm will, in addition to the in-centre ABC intervention, involve parental/guardian engagement in the promotion and incorporation of daily PA. Parents of preschoolers in this intervention arm will be given the option of participating in two online training sessions known as ‘webinars’ or be given hard copies of the training material. Similar to the provider sessions, the first parental session will be designed to increase awareness with regard to the importance of PA and highlight the dangers in falling prey to the commonly held belief that all preschoolers are vigorously active for a great portion of the day. The second session will expose parents to a variety of activities and provide practical tips and identify opportunities in which PA could be incorporated into a daily routine as well as demonstrate some simple games or play scenarios for small spaces, limited equipment, and outdoor play. Parents will be expected to login, via computer, to participate in these webinars, at their convenience, over the first week of the implementation of the intervention. A short and simple online questionnaire will be provided at the end of the webinars to ensure that the parents have completed the training and acquired the requisite knowledge to implement the home component of the program. Additionally parents will be provided with an ABC Child Activities Booklet outlining fun and simple physical activities to do with their children that require limited equipment. Parents will also receive bi-weekly postcards in the mail which will resemble materials from the *BusyBodies Activity Booklet* produced by the Ontario Public Health Association [55]. Our intent is to identify whether engaging parents is feasible and whether or not they will become involved in promoting PA during the time they spend with their children, and whether their involvement results in children’s increased PA compared to the DC only group.

#### Comparison

Participating daycare centres that are randomized to the wait list control will continue to provide their regular curriculum during the study period. All comparison centres will be offered the ABC trial staff training and resources after the completion of data collection.

The primary outcome (MVPA) will be measured at baseline and at 3-months and 6 months post-intervention. The trial assessments and timeline are illustrated in Table 1. The baseline measurement will occur 2 weeks before the workshops to providers and parental webinars. This will include an assessment of PA and sedentary behaviour, body composition, fundamental and gross motor movement skills, and an assessment of the physical environment in daycare centres and homes as perceived by providers and parents, as well as attitudes, control beliefs, quality of life, perceived competency and intentions of providers and parents toward incorporating PA into the daycare curriculum and home environment, respectively. Immediately following the workshop and webinar training, attitudes, control beliefs, perceived competence, and intentions toward incorporating PA into the daycare setting and home environment will be measured. The parents receiving webinar training will be given an on-line ‘test’ to make sure they understood the training material. The components of the theory of planned behaviour, plus an assessment of any physical changes to the daycare or home environment (perceived by the provider or parent) will also be assessed at 6 months to determine the extent to which they predict PA at different time points. The 3-month evaluations will include children’s PA and sedentary behaviour, body composition and movement skills, as well as an evaluation of quality of life. The 6-month evaluation will include all of the 3-month measures and questionnaires, in addition to evaluations of the physical environment and theory of planned behaviour variables to examine associations with children’s PA.

**Table 1 Tab1:** **Outcome assessments**

Activity Begins in Childhood (ABC)											
	Group 1: DC				Group 2: DC + HC				Group 3: COM		
	B	PW	3 mos.	6 mos.	B	PW	3 mos.	6 mos.	B	3 mos.	6 mos.
Consent Form	√				√				√		
Socio-Demographic Questionnaire	√				√				√		
Physical Activity Monitor Log	√		√	√	√		√	√	√	√	√
Environment Questionnaires					√		√	√			
EPAO	√		√	√	√		√	√	√	√	√
Gross Motor Assessment	√		√	√	√		√	√	√	√	√
Anthro Measures & Body Composition	√		√	√	√		√	√	√	√	√
Workshops/Webinar	√				√						
Workshop/Webinar Questionnaires	√	√		√	√	√		√			
Quality of Life Questionnaires	√		√	√	√		√	√	√	√	√
Pregnancy and Lifestyle Questionnaire	√				√				√		

B, baseline; mos, months; PW, post workshop; EPAO, Environment and policy assessment and observation.

### Assessment

#### Primary outcome variable

**Physical activity level** Physical activity levels of the preschoolers will be measured using omni-directional Actical^®^ accelerometers (mini Mitter Co., Inc., Bend, OR, USA). At each measurement period (baseline, 3- and 6-months post-workshop intervention), children will wear these activity monitors for a 7-day period. Study staff will train and assist the daycare providers and parents in correct placement of the accelerometer at the child’s time of arrival at the daycare centre on day 1. Data will be collected in 15-second epochs and Adolph et al.’s cut points [56] for preschool-aged children’s PA intensity will be applied to derive time spent at various intensities of movement (e.g., sedentary, light, moderate, vigorous) in harmony with the Canadian Health Measures Survey approach [57]. For ease of comprehension and comparison with other studies, activity data will be summarized and reported as activity minutes per hour, computed from tallied counts for each activity level mean across wear time. In line with current [57–59] and ongoing research in this population, [60] children with ≥5 hours of accelerometer data per day on at least 3 days will be included in the analyses and data will be adjusted for wear time.

### Secondary outcome variables

#### Fundamental/gross motor skills

The test of Gross Motor Development-2 (TGMD-2) will be used to evaluate the effects of the intervention on children’s movement skills [61]. The TGMD-2 is a validated standardized norm-referenced measure of 12 common gross motor skills of children ages 3 to 11 years [62]. The TGMD-2 evaluates 12 gross motor skills divided into two subtests: 1) locomotor (run, hop, gallop, leap, horizontal jump, and slide) and 2) object control (ball skills such as striking a stationary ball, stationary dribble, catch, kick, overhand throw, and underhand roll). This test will be conducted on participating children at baseline and 3- and 6-month assessments.

#### Anthropometrics

Height, weight, body mass index, lean body mass, fat mass, and percent body fat will be measured. Height will be measured using a portable stadiometer (Seca GmBH & Co Kg, Hamburg Germany). Body weight will be assessed using a Tanita scale (Tanita 300-A, Tanita Corporation of America, Inc., Arlington Heights, IL, USA). Body mass index (kg/m^2^) and body composition (lean body mass, fat mass, percent body fat) will be assessed using a RJL Quantum IV Bioelectrical Impedance Analyzer system (RJL Quantum IV, RJL Systems, Clinton Twp, MI, USA, 48035), which accommodates the small feet of young children and has been validated for preschool-aged ranges [63, 64]. This assessment takes about 3 minutes and will be conducted at baseline and 3- and 6-months post-intervention. Body composition measurement will be attempted at the same time of day in all measurement periods in attempt to control for liquid and food intake.

